### Study interventions

Participants will be randomly assigned (1:1:1) to one of the three groups for 8 weeks: (1) a 14:10 early TRF diet (eating ad libitum only between 8:00 AM and 6:00 PM) with probiotic supplementation; (2) an 14:10 early TRF diet (eating ad libitum only between 8:00 AM and 6:00 PM) with placebo supplementation; (3) a CR diet (energy-restricted 25% of required calories) with placebo supplementation as a control group.

During the TRF period, subjects are instructed to eat freely from 8:00 AM to 6:00 PM daily (for 10 h). While from 6:00 PM to 8:00 AM the next day (14 h), people will only be allowed to drink water, tea, and black coffee without sugar or any calorie-free drink. In addition, individuals will be suggested not to alter the composition of their usual diets throughout the TRF intervention. Furthermore, PCOS patients will be asked to consume a small handful of nuts consisting of 200 kilocalories of mixed nuts (18 g of fat, 5 g of protein, and 4 g of carbohydrates) during fasting if they experience drops in energy or severe headache [40].

In the CR diet of the control group, the daily calories will be calculated by a dietitian. Based on the Harris-Benedict formula, the basal metabolic rate (BMR) of patients will be calculated individually [41]. Then, the total daily energy needed by each person is calculated based on his physical activity and considering the thermogenic effect of food (TEF). Finally, 25% of the required calories [42] will be reduced. Subsequently, this daily caloric requirement will be divided into six-meal menus including 3 main meals and 3 snacks with a macronutrient ratio of 55% carbohydrates, 30% fat, and 15% protein. Based on this, a food menu will be prepared, and the necessary alternatives will be taught to the people of the control group. All participants will also take a probiotic or placebo supplement after breakfast with a glass of water.

### Randomization and blinding

A stratified permuted block randomization (a fixed block size of *n* = 6) was done using computer generated random numbers by the project coordinator. In this method, eligible patients who meet the study entry criteria are selected and then randomly allocated with stratification by BMI (between 25 and 30 and 30 and 35 kg/m^2^). People will be allocated to one of the three groups, IF diet with a probiotic supplement, IF diet with a placebo, and CR diet with a placebo. Random allocation will be based on a random number list; the letters A, B, and C will be assigned to an equal number of a random number list.

Placebo and probiotic supplements will be produced by TakGen Zist Pharmaceutical Company (Tehran, Iran) and will be placed in the same packages with similar color, flavor, and taste. Then packages will be placed in paper boxes and receive a special code. Placebo and probiotic supplement codes will remain with the company until the end of the study for blind researchers, laboratory staff, outcome assessors, and patients. However, no blinding will do in terms of diet (fasting or CR). In other hand, we do not anticipate any requirement for unblinding but if required, the trial manager, data coordinator, implementation support facilitators, and care home managers will have access to group allocations and any unblinding will be reported.

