## Subjects and methods

### Study design

The present placebo-controlled, parallel-arm, randomized, double-blind clinical trial examining the effects of IF diet alone or in combination with probiotic supplementation compared to the CR has been registered at the Iranian Registry of Clinical Trials (ID: IRCT20121110011421N5) on October 3, 2022. This trial will be performed at Arash Hospital, Tehran, Iran. Written informed consent will be obtained from participants before participation in the research project by researchers. We developed the study protocol based on the Standard Protocol Items: Recommendations for Interventional Trials (SPIRIT) 2013 checklist (Supplemental file 1). The timeline of the trial and study flow chart of enrolment, allocation, intervention, and assessment are presented in Table 1 and Fig. 1, respectively. A Standard Protocol Items: Recommendations for Interventional Trials (SPIRIT) diagram for the trial schedule is illustrated in Fig. 2. Any amendments to the present study protocol which have related to the safety and benefit of patients and the protocol deviations, unintentional alterations in study protocol that do not affect the subject’s rights, study’s risk or benefit, the integrity of data, and safety or welfare will require to be confirmed by Department of Clinical Nutrition and Medical Ethics Committee of Tehran University of Medical Sciences, Tehran, Iran, before the study conduction. Any alteration in the study protocol will be sent to the Trials journal (www.trialsjournal.biomedcentral.com).

**Table 1 Tab1:** Timeline of the trial

Explanation of the trial activities	Time (months)																	
	1	2	3	4	5	6	7	8	9	10	11	12	13	14	15	`16	17	18
Material preparation	*	*	*	*														
Recruitment					*	*	*	*	*									
Clinical assessments at baseline					*	*	*	*	*									
Nutritional assessments at baseline					*	*	*	*	*									
Biochemical assessments at baseline					*	*	*	*	*									
Intervention										*	*	*	*	*				
Clinical assessments after intervention										*	*	*	*	*				
Nutritional assessments after intervention										*	*	*	*	*				
Biochemical assessments after intervention										*	*	*	*	*				
Data analysis															*	*		
Writing the final report of the trial																	*	*
The expected time	*	*	*	*	*	*	*	*	*	*	*	*	*	*	*	*	*	*

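### Fixed blocks of 6 with an open diet would let staff who track allocations foresee the diet of up to about 27–29% of participants, and the double-blind label holds only for probiotic versus placebo within the TRF arms

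*Protocol article*

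**What the plan says.** On allocation, the Randomization and blinding section states: "A stratified permuted block randomization (a fixed block size of" 6), produced by the project coordinator from random numbers drawn by computer. Eligible patients are "randomly allocated with stratification by BMI (between 25 and 30 and 30 and 35 kg/m^2"). The three arms are "IF diet with a probiotic supplement, IF diet with a placebo, and CR diet with a placebo", in a 1:1:1 ratio (Study interventions: "Participants will be randomly assigned (1:1:1) to one of the three groups for 8 weeks").

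On blinding, the same section has the manufacturer keep the supplement codes until the end of the study, to blind researchers, laboratory staff, outcome assessors and patients. It then adds: "However, no blinding will do in terms of diet (fasting or CR"). The Study design section nevertheless describes a "placebo-controlled, parallel-arm, randomized, double-blind clinical trial", with no limit on what is blinded.

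The trial runs at one hospital (Study design). Two independent researchers recruit (Study participants and enrollment), and the project coordinator does the randomization.

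**The concern.** Two stated features work against each other. A single block size makes the end of every block predictable from its beginning, and an open diet makes the beginning visible. At one site, with two recruiters and diet known to the staff who coach participants, someone could follow the sequence of diets within a BMI stratum. If such a person also influenced who was enrolled and when, women judged more motivated could be steered towards one diet. Motivation is not measured, so no adjustment would remove that bias.

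The label raises a different problem. The stated aim is to compare TRF, alone or with probiotic, with the CR diet. In both of those contrasts the arms differ in something every participant and dietitian can see. CR is always paired with placebo, so anyone who knows the design also knows a CR participant's supplement, and the coded packs protect nothing there. Appetite, DASS-21, sleep quality, food craving and eating behaviour are self-reported, and acne is graded. Readers who take the label at face value would give these results more weight in the diet contrasts than an open comparison deserves.

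**Working it through.** The article gives no predictability figure to reproduce, so the calculation starts from its design inputs.

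*Inputs.* Block size 6, fixed; three arms at 1:1:1; two arms on TRF and one on CR; two BMI strata; diet open (Randomization and blinding, Study interventions). Total 90, at 30 per arm (Sample size calculation). *Assumption:* the observer knows the block size and every earlier diet in the stratum.

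*Step 1, block content.* 6/3 = 2 places per arm, so 4 TRF and 2 CR. The number of possible diet orders is 6!/(4!·2!) = 15, all equally likely.

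*Step 2, when the next diet is certain.* A place is certain when only one diet remains in the block. Counting over the 15 orders:

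| Place in block | Orders with TRF certain | Orders with CR certain | Share certain |
|---|---|---|---|
| 1 | 0 | 0 | 0% |
| 2 | 0 | 0 | 0% |
| 3 | 1 | 0 | 6.7% |
| 4 | 3 | 0 | 20.0% |
| 5 | 6 | 1 | 46.7% |
| 6 | 10 | 5 | 100% |
| Sum | 20 | 6 | 26/15 places per block |

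The closed form agrees: 4/(2+1) + 2/(4+1) = 4/3 + 2/5 = 26/15 = 1.733 places per block.

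*Step 3, share of participants.* 1.733/6 = 28.9%, and 0.289 × 90 = 26 participants. By diet, certain TRF is (20/15)/6 = 22.2% and certain CR is (6/15)/6 = 6.7%, about 6 of 90.

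*Step 4, incomplete last blocks.* Over every split of 90 between the two strata, the share lies between 27.1% and 28.9%. An even split gives the lower end: each stratum of 45 has 7 full blocks plus 3 places, so 2 × (7 × 26/15 + 1/15) = 24.4, and 24.4/90 = 27.1%.

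*Step 5, best guess.* An observer who always names the diet with more places left is right 4.467 times in 6, or 74.4%. Always naming TRF is right 4/6 = 66.7% of the time. The gain is just under 8 points.

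*Step 6, effect of varied blocks.* Simulation with 45 per stratum and an observer who knows the possible sizes but not their order gives the share of certain diets as 27.1% for fixed 6, about 10% for sizes 3 and 6, about 5% for 6 and 9, and about 4% for 3, 6 and 9.

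*Step 7, blinding by contrast.*

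| Contrast | Differs in diet (open) | Differs in supplement (coded) | Blinded? |
|---|---|---|---|
| TRF + probiotic vs CR + placebo | yes | yes | no |
| TRF + placebo vs CR + placebo | yes | no | no |
| TRF + probiotic vs TRF + placebo | no | yes | yes |

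The unqualified label in Study design fits one contrast of three, and that one is not among the comparisons with CR named in the aim.

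**The case against.** A reader might infer that recruiters did know about 29% of the diets, helped by publication of the block size. The article does not support that. It nowhere says that recruiters knew the block size, saw the list or followed earlier diets by stratum, and it places randomization and recruitment with different people. It is dated 25 October 2023, after the date by which recruitment was to be almost finished (23 September 2023, Trial status), so publication was hardly a route of exposure. Further detail on concealment may stand in the full protocol, and its absence here is no fault.

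Timing may remove the risk altogether. Table 1 puts recruitment in months 5–9 and intervention in months 10–14; if allocation waited until enrolment had closed, steering at enrolment could not arise. But the table does not settle this. It places baseline biochemistry in months 5–9, whereas the Biochemical assessment section draws baseline blood on the first day of the intervention, and Trial status gives about 11 months of recruitment against the table's five.

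The usable information is also smaller than the total suggests. Most of the certainty concerns TRF, already the likelier guess, and the supplement within TRF stays hidden. Nor would steering on weight be beyond repair: randomization is stratified by BMI, the primary outcomes are changes from baseline, and the planned mixed model adjusts for confounders. The irreparable part is confined to unmeasured traits.

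On the label, the Randomization and blinding section discloses the open diet, so a careful reader is not misled. The primary outcomes are weight on a digital scale and insulin resistance, and open assessment matters much less for these. Both points stand and limit the consequence, but the unqualified statement in Study design remains incorrect for the main question.

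**Conclusion.** The point holds in two limited parts.

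First, the fixed block of 6 with open diet allows the next diet to be known for at most about 27–29% of participants (about 24 to 26 of 90). That figure is conditional on knowing the block size and following all earlier diets in the stratum before each enrolment. It is an upper limit, not a rate shown to have occurred, and no selection bias has been demonstrated. The weakness lies in a stated design choice that is easily improved.

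Second, the double-blind description is wrong for both comparisons with CR. This part needs no assumption, since it follows from the article's own statement that diet is unblinded and from the pairing of CR with placebo. Its practical weight falls on the self-reported and rated secondary outcomes in the diet contrasts.

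**What to change.** For any allocations not yet made, generate the remaining list with randomly varied block sizes (for example 3, 6 and 9) within BMI stratum, and withhold the sizes from recruiting staff. The cost is regenerating the unused part of the list. The downside is a slightly larger possible imbalance: stopping inside a block of 9 can leave two arms 3 apart in a stratum, against 2 apart for a block of 6.

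If allocation is complete, as the recruitment dates suggest it may be, nothing can be changed in the list. Report the fixed block size together with the open diet as a limitation, and state whether recruiting staff knew the block size and the earlier diets.

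In either case, replace the unqualified label with wording such as: *double-blind for probiotic versus placebo within the TRF arms; open-label for diet*. Interpret appetite, mental health, sleep, craving, eating behaviour and rated skin outcomes in the CR contrasts as open-label. This costs only wording and alters neither the design nor the analysis.

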##### Anthropometric and blood pressure assessment

Body weight will be measured by fasting, without shoes, with minimal clothing, and using a digital scale (Seca, Hamburg, Germany) with a precision of 100 grams at baseline and 8 weeks during the intervention. The height of people will be measured to the nearest 0.5 cm while standing without shoes. BMI will be calculated using the formula of dividing weight in kilograms by the square of height in square meters. To measure blood pressure, patients were asked to rest for 10 min, then the measurement will be done using a mercury sphygmomanometer (Riester, Germany). The blood pressure of each person will be measured twice with a time interval of 10 min, in a sitting position. The average of these two measurements is considered as the patient's blood pressure.

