### Data management and monitoring

In the baseline and post-intervention phases, data will be collected. CRFs (case report forms) will be used for recording participant data. Data entry and management will be done using an electronic database after CRFs are used for data collection. There will be two data collectors, and completed clinical raw data will be sent for approval to the project supervisor. Documentation is kept in a locked drawer, only accessible by the principal investigator. The forms contain an ID number unique to the participant and do not contain any information that can be used to identify the patient.

A clinical trial monitor occasionally supervises the study progress and ensures patient rights and well-being are safeguarded; the protocol, ethical requirements, standards, and regulations are being followed; the essential documentation is available; and collected data are accurate as there were recorded. One of the investigators will check the coding, security, and storage of data. In addition, she will evaluate data entry and data values twice. If any participant reports the occurrence of adverse events, more information is required to make a decision about excluding the participants from the trial. Unblinding is permissible in this situation based on the Medical Ethics Committee criteria. Ethical review of the data will be overseen by the Tehran University of Medical Sciences. Further, patients who discontinue the study or deviate from it will be provided with a list of all outcome data. Missing data will be imputed using modern methods for dropouts.

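### Outcome assessors are blinded to the supplement but not to diet, which leaves hand-read blood pressure, and acne and hirsutism if an observer scores them, open to observer bias in both comparisons with the calorie-restricted arm

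*Protocol article*

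**What the plan says.** The Study design section describes "The present placebo-controlled, parallel-arm, randomized, double-blind clinical trial" and does not limit that label to one treatment component.

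The Randomization and blinding section gives the three arms as "IF diet with a probiotic supplement, IF diet with a placebo, and CR diet with a placebo". On masking it says: "Placebo and probiotic supplement codes will remain with the company until the end of the study for blind researchers, laboratory staff, outcome assessors, and patients". The next sentence reads "However, no blinding will do in terms of diet (fasting or CR". It exempts none of the four roles just listed, and no other section of the article restores masking to diet for anyone.

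On the outcomes concerned:

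- **Blood pressure.** Systolic and diastolic pressure are secondary outcomes, and "the measurement will be done using a mercury sphygmomanometer (Riester, Germany". Two seated readings are averaged.
- **Acne.** A secondary outcome, scored with a global grading system. The section Assessment of other variables does not say who does the scoring.
- **Hirsutism.** A secondary outcome with neither an instrument nor a rater given.
- **Primary outcomes.** Body weight, taken on a digital scale, and insulin resistance.

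On staffing, the Data management and monitoring section says "There will be two data collectors" and "The forms contain an ID number unique to the participant".

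**The concern.** Participants cannot be kept unaware of their diet, and neither can the dietitians who deliver it. The person who reads a blood pressure or grades skin can be. As written, the plan waives that safeguard for every role.

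The waiver falls on the comparisons that carry the trial's hypothesis, which is that TRF, alone or with the probiotic, does better than CR. An observer who knows the diet and expects TRF to work may read or grade differently by arm. The planned analysis (intention to treat, multiple imputation, mixed model, Benjamini-Hochberg q values) cannot remove a systematic measurement difference between arms.

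The unlimited double-blind label adds to this, because a reader would credit the TRF-versus-CR results with protection that the text does not give them.

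**Working it through.** **Step 1. What the supplement code masks.** Set the arms side by side:

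| Contrast | Differs in diet | Differs in supplement | Masked to the assessor by the code |
|---|---|---|---|
| TRF + probiotic vs TRF + placebo | no | yes | yes |
| TRF + placebo vs CR + placebo | yes | no | no |
| TRF + probiotic vs CR + placebo | yes | yes | only the supplement part |

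Both contrasts with the control can be told apart by diet alone.

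**Step 2. Which outcomes depend on an observer.**

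- Systolic and diastolic pressure: yes, documented as read on a mercury column.
- Acne and hirsutism: yes if an observer scores them, but the documents do not say so.
- Weight: a digital scale with a precision of 100 g leaves little room for judgement.
- Laboratory assays, including those behind insulin resistance: done on stored serum. The documents show no route by which knowledge of diet would alter them.

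**Step 3. An illustration of size.** The plan has no figure of its own to reproduce here. The documents give no size for an observer shift, so a range is assumed.

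Inputs: n = 30 per arm (Sample size calculation section), two-sided α = 0.05, true difference 0, and a differential observer shift of b standard deviations.

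For a two-sample t-test, df = 2n − 2 = 58, the critical value is 2.002, and the noncentrality is λ = b·√(n/2) = b·√15 = 3.873·b. The false-positive rate is P(|T| > 2.002), where T is noncentral t with 58 df and noncentrality λ.

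| Assumed shift b (SD) | λ | 30 per arm | 25 per arm |
|---|---|---|---|
| 0 | 0 | 5.0% | 5.0% |
| 0.1 | 0.387 | 6.7% | 6.4% |
| 0.2 | 0.775 | 11.9% | 10.7% |
| 0.3 | 1.162 | 20.8% | 18.0% |
| 0.4 | 1.549 | 33.2% | 28.3% |

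The λ column is for 30 per arm. The last column repeats the calculation with 25 per arm (df 48, critical value 2.011), the calculated size before allowance for dropout.

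**Step 4. The plan's own significance rule.** The Statistical analysis section requires P<0.05 and also q<0.1 by Benjamini-Hochberg. The family of tests is not stated. Assume 25 outcomes in it. An outcome that is the only rejection then needs P ≤ 0.1 × 1/25 = 0.004, and one that ranks fourth among the rejections needs P ≤ 0.1 × 4/25 = 0.016. With 30 per arm:

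| Assumed shift b (SD) | P<0.05 alone | P ≤ 0.016 | P ≤ 0.004 |
|---|---|---|---|
| 0.1 | 6.7% | 2.4% | 0.7% |
| 0.2 | 11.9% | 5.0% | 1.7% |
| 0.3 | 20.8% | 10.1% | about 4% |
| 0.4 | 33.2% | 18.5% | 8.3% |

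The q criterion lowers the rate, by an amount that depends on the family and on how many other outcomes are rejected. It does not correct the bias in the estimated difference.

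**The case against.** The strongest reply is that the diet sentence is terse and sits in a condensed article. It may mean only that the diet is open-label, with assessor procedures left to the full protocol. Nowhere does the text say that assessors will be told the diet. Part of this stands: a reader might infer that assessors will in fact know each woman's diet, and the documents do not establish that. But the sentence is a stated rule, not a silence. It follows directly on a list that includes outcome assessors, and it exempts none of them.

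Several stronger readings are tempting and are not supported:

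- **That the main results are compromised.** The primary outcomes are not shown to depend on the observer. The outcomes at risk are a few in a long secondary list.
- **That four secondary outcomes are observer-read.** This is documented only for systolic and diastolic pressure. For acne and hirsutism it is an inference.
- **That the laboratory is a source of bias.** No laboratory outcome is shown to be affected, and nothing says that the laboratory is told the diet.
- **That bias would favour TRF.** The hypothesis makes this plausible, but neither direction nor size is established.
- **That the trial's false-positive rate is 7% to 33%.** Those rates rest on an assumed shift, on P<0.05 alone and on all 30 per arm being analysed.

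A practical objection also stands in part. The article does not say what the two data collectors do. The section Adherence to the intervention has a researcher in daily contact about food, and dietary recalls are taken every two weeks. If both collectors share that work, both will learn the diet.

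**Conclusion.** The point holds in limited form. The article masks assessors to the supplement only, expressly leaves diet unmasked with no exception for them, and calls the trial double-blind without limit. In both TRF-versus-CR contrasts, systolic and diastolic pressure are open to observer bias. Acne and hirsutism are too, on condition that an observer scores them.

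No size can be read from the documents. The range of about 7% to 33% is illustrative and is an upper picture under the plan's own rule, because the added q<0.1 criterion lowers it. Body weight, insulin resistance and the laboratory assays are little exposed. This is a worthwhile correction to the measurement of secondary outcomes and to the description of the design. It is not a reason to doubt the primary comparison.

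**What to change.** Replace the sentence on diet blinding with wording such as:

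> Participants and dietitians are not blinded to diet. The data collector who takes end-of-study blood pressure and any observer-scored acne and hirsutism has no role in diet contacts or dietary recalls, sees only the participant ID, and asks participants not to reveal their diet.

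In the Study design section, limit the double-blind label to the supplement comparison. For assessments already completed, report whether the assessor knew the diet.

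**Cost.** No visit, sample size or treatment changes. Roles must be divided between the two existing data collectors; that this can be done is inferred from the Data management and monitoring section, not stated there. Some participants may still reveal their diet.

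The change may also come late. The Trial status section expects recruitment to be almost finished on 23 September 2023, and the article appeared on 25 October 2023. If each woman starts the 8-week intervention on enrolment, anyone enrolled by 30 August 2023 (56 days earlier) would have finished by publication. Prospective masking may then reach few participants, and for the rest the remedy is disclosure and the corrected label.
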